#### Chemoprevention Efficacy Cohort Study

This component will investigate the chemoprevention efficacy of SP+AQ at current dosing regimens among SMC-eligible children. Following the WHO’s Malaria Chemoprevention Efficacy Study Protocol [30], both malaria thick smears and dried blood spots (DBSs) will be taken at day 0, day 2, day 7, day 14, day 21, and day 28 during and after administration of the first cycle of SP+AQ, which will be administered through directly observed therapy. All DBS samples on day 0 and day 28 will be processed to ascertain low-density parasitemia estimates through qPCR. If sufficient DNA exists, day-0 and day-28 samples will be genotyped and compared. If children are found to have the same haplotype, this will indicate a recrudescent infection. If different haplotypes are present or if there is presence of an infection on day 28 that was not present on day 0, this will indicate a new infection after SP+AQ administration. Day-7 samples will also be processed for drug levels of all three SMC drugs, and day-28 samples will be processed for SP and AQ. The qPCR methodology is primed to detect presymptomatic parasitemia of clinical relevance. More sensitive PCR methodologies will not be conducted in order to prevent detection of extremely low–level parasitemia that will not be of clinical significance. DBSs will also be processed for estimates of blood parasite density and genotyping of relevant drug-resistance markers on days 2, 7, 14, and 21 if a child’s thick smear on those days was positive or if DBSs at a later time point are *P falciparum* positive. A DBS will also be collected whenever a child has a fever and is positive on a malaria RDT based on histidine-rich protein 2 and plasmodium lactate dehydrogenase. Drug level, qPCR parasite estimation, and genotyping will also take place. A blood smear will not be taken, as the RDT diagnosis will be sufficient when associated with fever. An RDT will not be given to children on day 0 unless they have signs and symptoms of malaria as per the standard SMC protocol, in which case they will be excluded from the study sample (see Figure 2 for an illustration of the proposed sample collection time points and subsequent sample processing sequence). We aim to recruit participants from within Lalaua, one of the new phase 2 research districts.

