#### Chemoprevention Efficacy Study

The primary outcome is chemoprevention failure in the presence of adequate drug concentration and associated parasite genotype, as defined by quantitative polymerase chain reaction (qPCR)–positive parasites on day 28 or a positive malaria slide at any time from day 7. Secondary outcomes include uncomplicated malaria within the first 28 days, hospitalization within the first 28 days, and severe malaria within the first 28 days.

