#### Chemoprevention Efficacy Cohort Study

Distributions and proportions of relevant mutations will be analyzed to compare the chemoprevention efficacy between groups of mutations. The blood drug concentrations will be analyzed as a cohort by mean, median, and SD, and statistical tests of their associations with treatment outcome—in particular, drug concentrations on day 7—will be performed. The focus will be on outliers with low levels of drug concentration based on the outcome measures described. Day-28 positivity will be associated with antimalarial drug resistance genotype.

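### Afebrile slide-positive failures on day 14 or 21 have a day-7 drug level but none at the time of failure, although the blood spot is already collected

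*Protocol article*

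**What the plan says.** All statements are in the protocol article.

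- **Outcome** (Primary and Secondary Outcomes, Chemoprevention Efficacy Study). The primary outcome is "chemoprevention failure in the presence of adequate drug concentration and associated parasite genotype". The events that count are a positive qPCR on day 28 or "a positive malaria slide at any time from day 7". Fever is not required. Neither a cut-off for adequacy nor the time at which the level is taken is given.
- **Sampling** (Recruitment and Data Collection, Chemoprevention Efficacy Cohort Study). Smears and "dried blood spots (DBSs) will be taken at day 0, day 2, day 7, day 14, day 21, and day 28".
- **Scheduled drug assays** (same section). "Day-7 samples will also be processed for drug levels of all three SMC drugs, and day-28 samples will be processed for SP and AQ".
- **Intermediate samples** (same section). If the smear is positive, or a later spot is positive, "DBSs will also be processed for estimates of blood parasite density and genotyping of relevant drug-resistance markers on days 2, 7, 14, and 21". Drug level is not in this list.
- **Unscheduled samples** (same section). "A DBS will also be collected whenever a child has a fever and is positive on a malaria RDT", and then "Drug level, qPCR parasite estimation, and genotyping will also take place".
- **Analysis** (Data Analysis, Chemoprevention Efficacy Cohort Study). Associations between concentration and outcome are to be tested, "in particular, drug concentrations on day 7".
- **Aim** (Study Design). The cohort is meant to show whether SP+AQ protects for 28 days and whether concentration and resistance affect how long protection lasts.

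**The concern.** Days 14 and 21 are scheduled points at which a primary failure can be detected, and they are also the points that describe how long protection lasts. For a child without fever who is slide-positive on one of those days, the plan obtains parasite density and genotype from that day's spot but not the drug level. For every other route to failure, the plan obtains a level at the time the infection is found.

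The outcome joins failure to adequacy of drug concentration, and the second objective asks how far resistance and concentration each account for reduced efficacy. A failure with drug still present points toward resistance; a failure after the drug has largely gone points toward short exposure. Without a level at failure, that distinction rests on the day-7 value alone for this one group. Because the outcome definition does not say which day's level decides adequacy, a reader cannot tell whether the day-7 value is meant to be enough.

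**Working it through.** **1. Reproduce the plan's own figure.** Inputs from Sample Sizes, Chemoprevention Efficacy Cohort Study: assumed rate 3%, n = 494, stated 95% CI 1.7% to 4.9%.

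Expected events: x = 0.03 × 494 = 14.82.

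Exact (Clopper-Pearson) limits: lower = Beta quantile (0.025; x, n − x + 1), upper = Beta quantile (0.975; x + 1, n − x). With x = 14.82 and n = 494 this gives 1.68% to 4.91%, which rounds to the stated interval. The sample-size statement is sound.

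**2. Expected number of failures.** Taking the assumed breakthrough rate as the failure rate:

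- lower limit: 0.017 × 494 = 8.4
- planned rate: 0.03 × 494 = 14.8
- upper limit: 0.049 × 494 = 24.2

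**3. Set the outcome definition beside the assay plan.**

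| How the infection is found | Drug level at that time? |
|---|---|
| Positive slide, day 7 | Yes, scheduled, all three drugs |
| Positive slide or qPCR, day 28 | Yes, scheduled, SP and AQ |
| Fever with positive RDT, any day | Yes, on the natural reading of the text |
| Positive slide without fever, day 14 or 21 | No; density and genotype only |

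**4. Distance to the nearest levels for the last row.** From day 7 to failure: 14 − 7 = 7 days, or 21 − 7 = 14 days. From failure to day 28: 28 − 14 = 14 days, or 28 − 21 = 7 days. The available levels therefore lie one or two weeks before failure and one or two weeks after it.

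**5. How many children this touches.** The documents do not give the share of failures that would be afebrile and slide-positive on day 14 or 21. As an assumed range applied to 14.8 failures:

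| Assumed share | Children |
|---|---|
| 10% | 1.5 |
| 25% | 3.7 |
| 50% | 7.4 |
| 75% | 11.1 |
| 100% | 14.8 |

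**6. Extra assays.** Counting one sample per failing child, the extra number cannot exceed the number of failures: about 15 at 3%, about 24 at 4.9%.

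**The case against.** The strongest reply is that the plan already has a concentration for these children. Every child is due a day-7 level of all three drugs, the analysis section singles out that day, and the outcome definition nowhere requires the level to be taken at failure. If adequacy is judged on day 7, every day-14 and day-21 failure can be classified. This stands. A reader might infer that these failures cannot be classified at all; the documents do not support that. What remains is that the outcome definition does not name day 7 as the deciding time point, and that the level at failure is missing for one failure type only.

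A reader might also infer that a day-7 level cannot stand in for a later one because concentrations fall in between. The documents give no half-lives. A decline common to all children would also leave their ranking on day 7 unchanged; the day-7 value misleads only to the extent that elimination differs between children, which nothing here quantifies.

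The absence itself is not certain. Figure 2, which illustrates the processing sequence, was not visible in the text reviewed, and the full protocol may add the assay. The sentence that adds a drug level for unscheduled samples has no explicit subject, so limiting it to febrile RDT-positive samples is the natural reading rather than the only one. Against this, the text does list what is done with positive day-14 and day-21 spots, and drug level is not on the list.

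Two further inferences go beyond the documents. One is that matched same-day comparators are needed for failure-day levels; that is a design preference, not the correction of an error. The other is that the wrong amodiaquine analyte is planned; the article uses drug names as shorthand and specifies no analyte.

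**Conclusion.** The point holds in limited form. Afebrile slide-positive failures on day 14 or 21 count toward the primary outcome and have a day-7 level, but the text plans no level at the time of failure, whereas failures found on day 7, on day 28 or through fever do have one. This weakens the attempt to relate concentration to duration of protection. It does not prevent the outcome from being classified, and it does not affect the sample size or the stated interval.

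The affected number lies somewhere between none and all of about 15 expected failures (8 to 24 across the stated interval); the documents do not narrow it. With so few failures, even a handful without a level at failure would be a noticeable share. The conclusion assumes that the 3% breakthrough rate is the failure rate, that the unscheduled drug level applies to febrile RDT-positive samples only, and that neither Figure 2 nor the full protocol adds the assay. It is a cheap improvement of minor to moderate severity.

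**What to change.** 1. In Recruitment and Data Collection, Chemoprevention Efficacy Cohort Study, add drug level to the processing of any slide-positive day-14 or day-21 blood spot.
2. In Primary and Secondary Outcomes, Chemoprevention Efficacy Study, state which time point's level defines adequacy. Keep the day-7 level as the exposure common to all children, so that failures and non-failures are compared on the same day.

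The cost is at most about 15 extra assays at the planned 3%, or about 24 at 4.9%, counting one sample per failing child. The spots are already collected and, when positive, already processed, so no visit or blood draw is added. The article reports that data collection ended in mid-June 2022, so the change depends on enough stored material remaining on those spots, which the article does not state. If it does not remain, the second change can still be made, and the missing failure-day levels can be reported as a limitation.

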**Figure 2 figure2:**
[figure not shown]
Proposed sample collection time points and subsequent sample processing sequence. DBS: dried blood spot; DOT: directly observed therapy; qPCR: quantitative polymerase chain reaction; SP+AQ: sulfadoxine-pyrimethamine plus amodiaquine.

#### Resistance Marker Study

Trends in SP and AQ resistance will be monitored in the two original intervention districts, as well as in the two research districts. Additionally, in the new phase 2 areas, the prevalence of *P*
*falciparum* plasmepsin 2 (*Pfplm2*) will be determined to inform future studies on appropriate use of dihydroartemisinin piperaquine for chemoprevention. A health facility–based, cross-sectional survey will be conducted before SMC project implementation (ie, baseline) and after one complete round of SMC distribution (ie, end line). Monitoring the prevalence of alleles associated with resistance to drugs is, by standard protocol, performed by collecting samples from symptomatic children with evidence of infection. The sample collection will be performed in four selected health facilities in each study district. The key markers to be monitored are as follows: *Pfdhfr*—codons 51, 59, 108, and 164; *Pfdhps*—codons 431, 437, 540, 581, and 613; *Pfcrt*—codons 72 to 76; *pfmdr1*—codons 86, 184, and 1246; and *Pfplm2*.

### Data Analysis

#### Cluster Randomized Controlled Trial

First, the characteristics of the eligible children in the intervention and control arms will be described and tabulated; these analyses will use survey weights obtained using population estimates for each community cluster. Next, a chi-square test will be performed to determine whether there is a significant difference in the proportions of children in each arm experiencing at least one confirmed malaria case during the study period, and exact odds ratios will be calculated.

Random-effects Cox proportional hazards regression models will then be fitted to estimate the difference in risk of an RDT-confirmed malaria case over time of follow-up; results will be expressed as hazard ratios, and a percentage effect size will be calculated. Model diagnostics will be run to verify the proportional hazards assumption, and random effects will be modeled at the community level to account for within-cluster correlation in malaria outcomes.

Two types of models will be fitted. The first will model risk of malaria based on time to first malaria case during each child’s first continuous period of follow-up; those experiencing an RDT-confirmed malaria case will be considered dropped from the sample, whereas those lost to follow-up will be considered right-censored. The second model type will account for recurrent events—using random effects for follow-up periods nested within individual children’s data—with children experiencing a malaria case considered to be “recovered” on the day of case confirmation and will continue to contribute follow-up information after this event.

Finally, to adjust for potential confounders, covariates based on data obtained from the baseline recruitment survey will be added sequentially to each of these two models by forward stepwise selection.

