### Sample Sizes

#### Cluster Randomized Controlled Trial

Clusters will be selected for the intervention arm at the community level in two districts. The study will be powered to have an 80% chance of detecting a significant reduction in RDT-confirmed malaria incidence at the 5% confidence level using a chi-square test comparing two independent proportions in a cluster randomized design. We are aiming to detect a significant reduction in malaria incidence from 0.2 to 0.12 clinical episodes per child per high-transmission season, corresponding to the SMC round. The clinical episodes should be of sufficient severity to present to a health facility, and the reduction in episodes should be equivalent to an odds ratio of 0.66, or a minimum effect size of 33%. This is based on the assumption that the efficacy of SP+AQ in Northern Mozambique, where the prevalence of resistance alleles in circulating parasites is high, is half of that found in studies in West African settings. To account for the cluster randomized design, we assumed an intracluster correlation for malaria outcomes within communities of 0.23, based on data from SMC coverage surveys conducted by the Malaria Consortium in 2020 [27] and 2021 [28]. A cluster size of 15 children per community was selected, and children in the intervention and control arms were recruited in a ratio of 1:1.5. This resulted in a total sample size of 2850 eligible children in 190 clusters: 1710 in 114 clusters in the control arm and 1140 in 76 clusters in the intervention arm. A total of 76 communities from a list of all communities will be selected as intervention districts using a simple random method. Then, 114 communities will be selected at random from among those remaining for inclusion in the control arm.

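### The chi-square test and exact odds ratios comparing the arms make no allowance for community clustering; at the planning ICC of 0.23 this step has about 34% type I error instead of 5%

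*Protocol article*

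**What the plan says.** In the protocol article, Sample Sizes (Cluster Randomized Controlled Trial), communities are the unit of allocation: 76 are drawn at random for intervention, then 114 of the remainder for control. The trial is sized "using a chi-square test comparing two independent proportions in a cluster randomized design". On clustering, the section says "we assumed an intracluster correlation for malaria outcomes within communities of 0.23", with 15 children taken per community.

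Data Analysis (Cluster Randomized Controlled Trial) then runs in this order:

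- Baseline description by arm, with survey weights tied to those tabulations.
- The comparison of arms: "a chi-square test will be performed to determine whether there is a significant difference in the proportions of children in each arm", the outcome being at least one confirmed case during the study. With it, "exact odds ratios will be calculated".
- Random-effects Cox models, one for time to first case and one for recurrent cases. For these, and only these, the section says that correlation within communities is handled, through a community random effect.
- Covariate adjustment added to the Cox models.

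No analysis is named as primary. Under Primary and Secondary Outcomes, the primary outcome is the incidence of RDT-confirmed cases found by passive surveillance.

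**The concern.** A chi-square test on individual children, and standard exact methods for a two-by-two table, treat every child as independent. Children in one community share exposure, access to care and arm. With a sizeable ICC, the difference between arms varies by chance far more than those methods allow. The p-value is then too small, and any interval around the odds ratio is too narrow.

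The survey weights do not repair this. The text ties them to the descriptive tables, and weights alone do not bring intracluster correlation into a variance.

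At stake is the first significance statement the trial would make about its arms. The plan sizes the trial for clustering and then writes a test that leaves clustering out. The result could also disagree with the cluster-adjusted Cox models, and the article does not say which would prevail.

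**Working it through.** **Inputs** (Sample Sizes, Cluster Randomized Controlled Trial): proportions 0.20 and 0.12; 5% level, taken as two-sided because the article does not say; power 80%; ICC 0.23; 15 children per community; 1140 intervention and 1710 control children in 76 and 114 communities.

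**Step 1. Reproduce the plan's sample size.**

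- Allocation is 1 intervention to 1.5 control, so the pooled proportion is (1.5 × 0.20 + 0.12)/2.5 = 0.168.
- Control children before inflation: [1.96 × √(2.5 × 0.168 × 0.832) + 0.8416 × √(0.20 × 0.80 + 1.5 × 0.12 × 0.88)]² / 0.08² = (1.1586 + 0.4749)² / 0.0064 ≈ 417. Intervention: 417/1.5 = 278. The total is 695.
- Design effect: 1 + (15 − 1) × 0.23 = 4.22.
- Inflated: 417 × 4.22 ≈ 1760 control and 1760/1.5 ≈ 1173 intervention, total 2933. The stated total is 2850, a difference of 2.9%.
- Power at the stated numbers, using effective sizes 1710/4.22 ≈ 405 and 1140/4.22 ≈ 270: 78.8%.

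The stated total is therefore recovered, to within 3%, only with the design effect applied. Without it, about 695 children would do. The powered test is a cluster-adjusted one.

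(The section also calls the effect an odds ratio of 0.66 or a 33% reduction. A fall from 0.20 to 0.12 is an odds ratio of 0.545 and a 40% reduction. That is a separate matter and does not enter the type I error below.)

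**Step 2. Standard error in the analysis as written.**

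- Ratio of true to naive standard error: √4.22 = 2.05.
- Under no effect at prevalence 0.20, the naive standard error of the difference is √[0.16 × (1/1710 + 1/1140)] = 0.0153. Allowing for clustering it is 0.0153 × 2.05 = 0.0314.
- The unadjusted test therefore declares significance at a difference of about 1.96 × 0.0153 = 3.0 percentage points, where 1.96 × 0.0314 = 6.2 points is needed.

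**Step 3. Type I error of the unadjusted test:** 2 × [1 − Φ(1.96/√DE)], where DE = 1 + 14 × ICC.

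| ICC | Design effect | Type I error |
|---|---|---|
| 0.02 | 1.28 | 8% |
| 0.05 | 1.70 | 13.3% |
| 0.10 | 2.40 | 20.6% |
| 0.20 | 3.80 | 31.5% |
| 0.23 (planned) | 4.22 | 34.0% |
| 0.30 | 5.20 | 39.0% |

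**Step 4. Check by simulation.** Beta-binomial data were generated with no effect, 114 and 76 clusters of 15, ICC 0.23, and 20,000 replicates. The unadjusted test rejected in 34.3% at prevalence 0.20, 34.0% at 0.12 and 33.6% at 0.168. With a continuity correction the figure was about 32%. Dividing the chi-square statistic by the design effect brought rejection back to 4.9%.

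**The case against.** The strongest reply is that the article never says the chi-square is unadjusted. Its sample size section names a chi-square in a cluster design, so the analysis section may mean that same test, with the variance method left to the full protocol or the SAP. This does not hold up well. The analysis section does address clustering, but only for the Cox models, and the exact odds ratios named beside the chi-square ordinarily assume independent children. As written, this is a named method that does not fit the design rather than a detail left out for brevity.

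Three other points stand and limit the finding.

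- **Scope.** A reader might infer that the trial has no valid comparison of arms, or that between-community variation alone could carry its conclusion. The documents do not support that, since the Cox models of confirmed malaria that follow include community random effects.
- **Status.** A reader might infer that the chi-square is the primary analysis, or that correcting it means making the Cox models secondary. The article names no primary analysis. Its primary outcome is incidence, which the Cox models, especially the recurrent-event one, address at least as directly as the proportion with any case.
- **Size.** The ICC of 0.23 is a planning value drawn from SMC coverage surveys, while the outcome is cases presenting at health facilities. The realised ICC may be lower, and the error with it.

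**Conclusion.** The point holds for the chi-square and exact odds ratio step, and for that step only. At the plan's own ICC and cluster size its two-sided type I error is about 34% against a nominal 5%, with the standard error understated about 2.05-fold. At an ICC of 0.05 the error would be about 13%, and at 0.02 about 8%.

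These figures assume equal clusters of 15, a two-sided 5% test, and that the absence of any stated adjustment means there is none. The step deserves correction despite the sound models after it, because the text gives it the job of determining significance and the sample size rests on the cluster-adjusted version of the same test. The finding does not establish that the trial as a whole would reach a false conclusion.

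**What to change.** Either of two changes is enough:

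1. Replace the chi-square and exact odds ratios with a cluster-adjusted comparison of the same proportion. A design-effect-adjusted or Rao-Scott chi-square would serve, as would a GEE or mixed logistic model with community as the cluster.
2. Keep them, label them crude, and state that the significance conclusion comes only from a cluster-adjusted analysis, such as the community-random-effects Cox model already planned.

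Which cluster-adjusted analysis is primary remains the sponsor's choice. The change takes one sentence and no new data. Confidence intervals for this comparison become wider. Under the first option, power with the design-effect-adjusted chi-square at the stated sample size is about 79% for 0.20 against 0.12, close to what the plan intended.

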### Objectives

Phase 2 aims to test the feasibility, effectiveness, and chemoprevention efficacy of SMC with SP plus AQ (SP+AQ) in Nampula Province in Mozambique, where malaria transmission is highly seasonal. Specific objectives include the following:

To determine the effectiveness of SMC in reducing the incidence of malaria infection among children aged 3 to 59 months.To determine and measure efficacy as follows:To determine chemoprevention efficacy of SP+AQ when used for SMC in Nampula Province, Mozambique.To calculate the extent to which efficacy is impacted by drug resistance and drug concentrations.To investigate the presence and change of SP+AQ– and piperaquine-resistance markers over time as a result of SMC implementation.To understand the impact of the SMC implementation model by determining process, costing, and acceptability outcomes for the intervention.

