## Methods

### Study Design

This type 2, hybrid, effectiveness-implementation study uses a convergent mixed methods approach [26]. As the study includes components of clinical effectiveness and implementation research, a type 2, hybrid, effectiveness-implementation design was selected. These designs provide benefits over pursuing these lines of research independently; for example, they offer more rapid translational gains, more effective implementation strategies, and more useful information for decision makers. SMC will be implemented in four monthly cycles between January 2022 and April 2022 in four districts of Nampula Province (Figure 1): Malema and Mecubúri, where phase 1 of the study was conducted, will continue to receive SMC in phase 2; Lalaua, the control area in phase 1, and Muecate will receive SMC for the first time in phase 2. The research will involve the following components:

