### Recruitment and Data Collection

#### Cluster Randomized Controlled Trial

In the control arm in both districts, compounds will be randomly sampled by researchers using household lists from selected communities, with one eligible child recruited at random from each household. After caregivers provide consent, children will be recruited and a short baseline questionnaire will be administered to collect individual data on each child and to confirm their eligibility. In the intervention arm, a researcher will follow a pair of community distributors as they administer SMC. In addition to variables such as experiences of fever within the past month among selected children, data on a range of variables relating to the selected child, their caregiver, and their household will be collected as part of the survey. These variables will include the selected children’s age, sex, and use of mosquito nets as well as the caregivers’ and heads-of-household’s level of education, occupational position, literacy level, household size, wealth (using the Simple Poverty Scorecard), primary language, and migration status, among other variables. Data on these variables will be collected in order to include potential confounders in the analysis for the association between the receipt of SP+AQ and clinically significant malaria. Children will be given SP+AQ by community distributors via directly observed therapy; in addition, blood samples will be taken and subsequent hemoglobin concentration measured using a HemoCue system (HemoCue AB). Children recruited into the study presenting at clinics will be identified using unique identification numbers and barcodes, and data on clinic visits, including suspected malaria cases and results of RDTs, will be matched to baseline questionnaire data to build a database for analysis.

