## Results

Data collection began in mid-January 2022 and concluded in mid-June 2022. Data analysis is expected to be completed by October 2022.

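### The Cox models appear to run on each child's own follow-up clock although transmission is highly seasonal and nothing requires the two arms to enrol over the same dates; calendar time with delayed entry would be the safer axis

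*Protocol article*

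**What the plan says.** Data Analysis, Cluster Randomized Controlled Trial, fits random-effects Cox models "to estimate the difference in risk of an RDT-confirmed malaria case over time of follow-up". The first model takes "time to first malaria case during each child’s first continuous period of follow-up"; the second extends this to recurrent cases. No time origin, calendar axis, delayed entry or adjustment for date is mentioned. A chi-square test and odds ratio on the proportion with at least one case come before these models.

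Recruitment and Data Collection describes two enrolment processes. For the treated communities: "In the intervention arm, a researcher will follow a pair of community distributors as they administer SMC". For the controls: "compounds will be randomly sampled by researchers using household lists from selected communities". The first is tied to SMC delivery days. The second has no stated date or cycle.

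The Objectives describe the province as one "where malaria transmission is highly seasonal". On the calendar, Study Design says "SMC will be implemented in four monthly cycles between January 2022 and April 2022" (the Abstract gives December 2021 to March 2022), and Results says "Data collection began in mid-January 2022 and concluded in mid-June 2022".

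**The concern.** A Cox model compares, at each event, the children at risk at the same point on the chosen time axis. On a follow-up axis these are children on the same day since enrolment, whatever the date. If one arm starts later, day 30 in one arm falls in a different part of the season from day 30 in the other, and the seasonal difference enters the treatment contrast.

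Randomising communities does not protect against this, because entry dates are set after allocation by procedures that differ between arms. A community random effect does not remove a systematic difference between arms. Enrolment date is not among the baseline covariates named; that list is open-ended and selection is stepwise, so adjustment for date is possible but not assured.

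At stake is the effect estimate for the trial's primary outcome. The direction of any bias depends on whether transmission is rising or falling, and on which arm starts first.

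**Working it through.** **Inputs from the article.** The plan gives no figure for the time axis, so there is none of its own to reproduce. The check uses the target "reduction in malaria incidence from 0.2 to 0.12 clinical episodes per child per high-transmission season", the arm sizes in Sample Sizes (1710 control, 1140 intervention), and a window of about 150 days from mid-January to mid-June. Treating 0.20 and 0.12 as cumulative risks, as the plan's two-proportion calculation does, the implied hazard ratio is

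ln(1 − 0.12) / ln(1 − 0.20) = 0.1278 / 0.2231 = 0.573.

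**Assumptions, none given in the article.** Common end date; control risk 0.20 over the full window; entry in each arm spread over 14 days; controls starting 0, 7, 14 or 28 days after the intervention arm; constant true hazard ratio; community random effects left out. The seasonal hazard is

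h(t) ∝ 1 + (r − 1) × ½ × [1 + cos(2π(t − p)/300)],

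with peak day p = 15, 75 or 135 and peak-to-trough ratio r = 1, 2, 3 or 5.

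**Mechanism.** With entry date e and control lag L, the follow-up axis at day s compares HR × h(e + s) with h(e + L + s). The apparent ratio is HR × h(e + s)/h(e + L + s). On the calendar axis both arms share h(t), which cancels.

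**Calculation.** The large-sample Cox estimate solves

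Σ { d_I(s) − [d_I(s) + d_C(s)] × R_I(s)e^β / [R_I(s)e^β + R_C(s)] } = 0,

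where R and d are the expected numbers at risk and with an event in each arm. It was solved once with s as days since enrolment and once with s as calendar date with delayed entry.

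**Results for true HR 0.573, r = 3.**

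| Control lag | Follow-up axis, peak day 15 | Peak day 75 | Peak day 135 | Calendar axis, any peak |
|---|---|---|---|---|
| 0 days | 0.573 | 0.573 | 0.573 | 0.573 |
| 7 days | 0.599 | 0.573 | 0.549 | 0.573 |
| 14 days | 0.628 | 0.574 | 0.526 | 0.573 |
| 28 days | 0.696 | 0.578 | 0.478 | 0.573 |

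As a ratio to 0.573, the 14-day extremes are 0.526/0.573 = 0.92 and 0.628/0.573 = 1.10; the 28-day extremes are 0.478/0.573 = 0.83 and 0.696/0.573 = 1.21. Across r = 2 to 5, the 28-day range is 0.454 to 0.738. With a flat hazard (r = 1) the follow-up axis gives 0.573 at every lag.

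With no true effect and r = 3, the follow-up axis gives 0.916 to 1.094 at 14 days and 0.832 to 1.213 at 28 days. The calendar axis gives 1.000 throughout.

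**How far the mid-window result reassures.** With p = 75 the hazard at either edge of the window is 1 + 2 × ½ × (1 + cos 90°) = 2 against 3 at the peak, so it varies only 1.5-fold, and rising and falling halves offset each other. A separate simulation used a 16-week round, a bell-shaped season, a true HR of 0.60, intervention enrolment within 5 days and controls spread over 28. It gave 0.63 with a mid-round peak, 0.73 early and 0.54 late. The calendar axis gave 0.60 in all three, and both axes agreed when controls also enrolled within the 5 days.

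**Cost in precision.** At a 28-day lag (r = 3, HR 0.573), the standard error of the log hazard ratio, ignoring clustering, goes from 0.112 to 0.120 with an early peak and from 0.113 to 0.108 with a late peak.

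**The binary comparison.** Clinic visits are linked through study identifiers issued at recruitment, so cases before enrolment are presumably not captured and later entry means less time at risk, even without seasonality. At HR 0.573 and flat hazard, the odds ratio moves from 0.547 with no lag to 0.613 at 14 days and 0.695 at 28. With no true effect and r = 3 it is 1.06 to 1.17 at 14 days and 1.14 to 1.41 at 28. The Cox time axis does not affect this.

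**The case against.** The strongest reply is that two silences in a condensed article are being read as a defect. The time origin is not named, and the full protocol or analysis plan may fix it. The control-arm text says how children are sampled, not when, and the intervention text does not say at which cycle enrolment takes place. A reader might infer that the arms were enrolled at different times and that the trial's hazard ratio is therefore biased. The article supports neither step: no enrolment gap is recorded, and with simultaneous enrolment the two axes give the same answer.

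The larger figures also need a peak near one end of the window. SMC is aimed at peak transmission, which suggests something more central, where the bias is small. That reassurance is incomplete: a January to April round centred on the peak would put it around the start of March, ahead of the midpoint of a mid-January to mid-June window. This too is inference, since those data collection dates cover all components.

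On the chi-square test, the article refers to one study period for both arms, so unequal time at risk arises only if entry dates differ. Starting the count at a common date would discard early cases, including those soon after the first observed dose, and so change what is measured. That objection stands against replacing the main binary comparison.

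What remains is that the article does describe a per-child follow-up axis in a strongly seasonal setting, with arm-specific enrolment and no safeguard on dates. That goes beyond a missing detail, because a better axis is available and loses nothing when the dates coincide.

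**Conclusion.** The concern holds as a conditional one. The described axis leaves the hazard ratio open to seasonal confounding if enrolment dates differ between arms, and the article states nothing that rules this out. For controls entering later, with the assumed threefold curve, the estimate is off by up to about 10% at 14 days and 17% to 21% at 28 days when the peak is near an edge of the window. It is off by less than 1% with a mid-window peak, and not at all with simultaneous entry or flat hazard. The sign is unknown in advance, and earlier control entry would reverse it. The sizes rest on assumed lags and curves, not on trial data.

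A reader might also infer that a calendar axis is free and settles everything. It is not quite free, since person-time when only one arm is at risk stops contributing, and it leaves the crude odds ratio untouched. The change is worth making in the analysis, with medium confidence that it would matter in practice.

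**What to change.** In Data Analysis, Cluster Randomized Controlled Trial, state that both Cox models use calendar date as the time axis and that each child enters the risk set on the enrolment date (delayed entry). Enrolment and case dates are needed for the models anyway, so no new data are required. The costs are the small change in standard error and the loss of information from periods when only one arm is at risk.

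Tabulate enrolment dates by arm and district, which shows directly whether a gap occurred. Keep the proportion with at least one case as planned, and add a sensitivity analysis counting cases in both arms from a common date per district, set after enrolment has closed in both arms. That analysis loses the earlier cases, which is why it should accompany the main comparison and not replace it. Since Results reports data collection as complete, the remedy now lies in the analysis.
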